#### Blinding

We will aim to maintain a blind status for as many people involved in the study as possible. Professionals carrying out the intervention will not be informed about a patient’s enrolment in the study until the start of the intervention. During data analysis, researchers will be blinded to the group assignment. Due to ethical considerations, it will not be feasible for interviewers collecting the data and participants to be blinded to group assignment. All participants will be informed about the starting time of the intervention, and will at all times be aware of their group status.

### Economic evaluation

The economic evaluation will be performed from a societal perspective. We will consider all relevant direct and indirect costs, such as costs of the care model, consultations with primary care physicians, medical specialists, home care, medication use, hospital and nursing home admissions, informal care time and cost of lost labour days of the informal caregiver. Care utilization data of both the client and the caregiver will be prospectively collected alongside the trial using six monthly cost diaries. Medication data of clients will be obtained from the centralized pharmacy files in the research regions. Dutch standard costs are used to value resource use [40,41]. Medication costs will be valued using prices of the Royal Dutch Society for Pharmacy [42]. Lost productivity costs will be calculated according to the friction cost approach (friction period 154 days) using the mean age and sex specific income of the Dutch population [40,43]. We will calculate a cost price for the care model using a bottom-up approach. The EuroQol (EQ-5day) [27] will be used to measure health-related quality of life. We will estimate utilities with the Dutch tariff developed by Lamers et al. [44] and then calculate Quality Adjusted Life Years (QALYs).

Missing data on costs and outcomes will be imputed using multiple imputation according to the Multivariate Imputation by Chained Equations (MICE) algorithm [45]. A cost-effectiveness (CE) analysis will be performed comparing the difference in total mean costs to the difference in quality of life, functional status and care needs; a cost-utility (CU) analysis will be used to estimate the incremental costs per QALY. Uncertainty around the incremental CE and CU ratios will be estimated using the bias-corrected percentile bootstrapping method (5000 replications) and will be plotted in cost-effectiveness planes. In addition, cost-effectiveness acceptability curves and net monetary benefits will be estimated to show the probability that the geriatric care model is cost-effective in comparison with usual care using different ceiling ratios [46]. Sensitivity analysis will be done to assess the robustness of the results and will include the most important cost drivers.

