## Methods

### Study design and setting

We will implement the geriatric care model using a stepped-wedge cluster randomised clinical trial design. A stepped wedge design is a type of cluster randomized trial design involving sequential roll-out of an intervention to primary care practices (clusters) over a number of time periods [21]. Primary care practices in the control group offer usual care, whereas practices in the intervention group deliver care according to the geriatric care model. By the end of the study, all practices will have started with the intervention. The trial will run over a 24-month period, and will be conducted among a total of 35 primary care practices in the Netherlands, with practices distributed among the regions Amsterdam (18 practices) and West-Friesland (17 practices). The Amsterdam region is of an urban nature, whilst the West- Friesland area can be characterized as an urbanised rural setting. Following participant inclusion, effect measurements will be administered at baseline and at 6, 12, 18, and 24 months (Figure 1). The study received approval by the medical ethics committee of the VU University medical centre. Participants will enrol only after a signed declaration of informed consent.

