### Effect evaluation

The primary outcome of the study is quality of life as measured by the 12-item Short Form questionnaire (SF-12) [26]. The SF-12 measures quality of life in two domains: a mental health component score (MCS) and a physical health component score (PCS). All outcome measures are presented in Table 1.

**Table 1 T1:** Overview of outcomes, baseline measurements and follow-up measurements

**Older adults**		**Instrument**	**Baseline**	**6 Months**	**12 Months**	**18 Months**	**24 Months**
**Patient outcomes**	1. Quality of Life	SF-12 [26]	**x**	**x**	**x**	**x**	**x**
	2. Health-related Quality of Life	EuroQol (EQ-5D) [27]	**x**	**x**	**x**	**x**	**x**
	3. Independence in ADL	Katz ADL index [28]	**x**	**x**	**x**	**x**	**x**
	4. Psychological Wellbeing	RAND-36 subscale [29]	**x**	**x**	**x**	**x**	**x**
	5. Social Functioning	1 item on RAND-36 scale	**x**	**x**	**x**	**x**	**x**
	6. Self-reported Health	2 items on RAND-36 scale	**x**	**x**	**x**	**x**	**x**
	7. Acute Hospital Admissions	1 item of our data set and Cost Dairies	**x**	**x**	**x**	**x**	**x**
**Quality of Care**	8. Care Needs	CANE [30]	**x**		**x**		**x**
**Process Outcomes: Achieved transition**	9. Patient-reported Client-centred Care	CCCQ [31]	**x**	**x**	**x**	**x**	**x**
	10. Coordination of Care from the patient’s perspective	2 items on QUOTE [32]	**x**	**x**	**x**	**x**	**x**
**Informal Caregivers**		**Instrument**	**Baseline**	**6 Months**	**12 Months**	**18 Months**	**24 Months**
**Carer outcomes**	12. Quality of life	SF-12	**x**	**x**	**x**	**x**	**x**
	13. Self-rated Burden of Care	CarerQol [33]	**x**	**x**	**x**	**x**	**x**
**Older adults and informal caregivers**		**Instrument**	**Baseline**	**6 Months**	**12 Months**	**18 Months**	**24 Months**
**Costs**	Direct and Indirect Costs	Cost diaries					

*SF-12* Short Form-12 questionnaire; *EuroQol (EQ-5D)* measures of 5 dimensions of health-related quality of life; *Katz ADL* Katz Activities of Daily Living; *RAND-36* measure of health-related quality of life; *CANE* Camberwell assessment of needs in the elderly; *Arm 1-4* allocation arm number 1–4; *CCCQ* Client-centred Care Questionnaire; *QUOTE* QUality Of care Through the patient’s Eyes; *CarerQol* care-related quality of life of informal caregivers

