#### Analyses

First, characteristics of the participants at baseline will be described and differences between the 4 allocation arms are tested using chi-square tests and ANOVA or non-parametric tests.

Second, effect analyses will be done based on the “intention-to-treat” principle. For both older adults and their primary caregivers, all outcome measures will be compared between the group receiving the geriatric care model and the group receiving usual care using multilevel regression analysis. Multilevel regression analysis takes into account the non-independent nature of hierarchical data and does not require data for a fixed number of observations for all respondents [38]. In the present study, three levels can be distinguished. Repeated observations are clustered within the patient and the patients are clustered within the primary care practices. Potential confounding (due to baseline differences) and effect-modifying will be accounted for during the analysis. If necessary an adjustment will be made for baseline differences between the groups.

In addition to the investigation of the overall effect of the intervention, the stepped-wedge design allows us to study the effects of the duration of the intervention on outcome measures [39]. Therefore, in additional analysis, the interaction between time and intervention will be added to the analyses.

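### The economic evaluation fixes no baseline adjustment for QALYs and effects, and the only adjustment rule in the article is conditional

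*Protocol article*

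**What the plan says.** The Economic evaluation section sets out its own chain of steps. Missing costs and outcomes are imputed by chained equations. The cost-effectiveness analysis proceeds by "comparing the difference in total mean costs to the difference in quality of life, functional status and care needs". For QALYs, "a cost-utility (CU) analysis will be used to estimate the incremental costs per QALY", with utilities from EQ-5D and the Dutch tariff. A bias-corrected percentile bootstrap with 5000 replications then feeds the cost-effectiveness planes, with acceptability curves and net monetary benefits alongside. No regression model or covariate is named for the effect or QALY difference.

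The Analyses section, under Effect evaluation, says that "all outcome measures will be compared between the group receiving the geriatric care model and the group receiving usual care using multilevel regression analysis". It adds that potential confounding from baseline differences will be accounted for, and ends with "If necessary an adjustment will be made for baseline differences between the groups". It does not mention QALYs, cost ratios or the bootstrap.

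Under Study design and setting, "effect measurements will be administered at baseline and at 6, 12, 18, and 24 months". Table 1 schedules EQ-5D, SF-12 and Katz at all five of these points, and CANE at baseline, 12 and 24 months. A baseline value is therefore planned for every effect that is set against costs.

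**The concern.** A QALY total is an area under the utility curve, and that curve starts at the baseline utility. A baseline gap between groups enters the total directly. It also enters indirectly, because people with a high utility at entry tend to have high utilities later. Only 35 practices are randomised, by region, to four arms, so some baseline gap is expected by chance.

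If the QALY difference is not adjusted, part of what the cost-utility ratio, the planes and the acceptability curves show is who happened to be recruited where. If adjustment is decided after the baseline comparison has been seen, the estimator depends on the data, and the precision that the baseline value offers is used only sometimes.

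**Working it through.** **Inputs from the protocol article.** Sample size calculations: SD 7.1 (PCS) and 6.6 (MCS); correlation of repeated measurements 0.66 (PCS) and 0.5 (MCS); intra-cluster correlation (ICC) 0.02; 33 participants per practice; 4 follow-up measurements; difference 3 points; alpha 0.05; power 90%; attrition 20%. Table 1: EQ-5D at 0, 6, 12, 18 and 24 months. The article gives no SD, correlation or expected gain for EQ-5D or QALYs.

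**The plan's own figure.** Sample size per arm = 2(1.960 + 1.282)² SD² [1 + 3ρ] / (4 × 3²), times the design effect 1 + 32 × 0.02 = 1.64, divided by 0.8.
- PCS: 87.69 × 1.64 / 0.8 = 179.8, so 180.
- MCS: 63.57 × 1.64 / 0.8 = 130.3, so 131.

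Both match the article. The correlations used below are therefore the ones its calculation rests on, though they belong to SF-12.

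**24-month QALY per person.** Assume that EQ-5D has the SF-12 correlations and that all pairs of time points correlate equally. The trapezoid weights on the five utilities are w = 0.25, 0.5, 0.5, 0.5, 0.25, so Σw = 2 and Σw² = 0.875. In units of the utility variance:
- variance of the QALY = 0.875 + ρ(4 − 0.875)
- covariance with baseline utility = 0.25 + 1.75ρ
- R² = covariance² / variance
- SE unadjusted / SE adjusted = 1/√(1 − R²)

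| ρ | Variance | Covariance (slope) | R² | SE ratio |
|---|---|---|---|---|
| 0.5 | 2.4375 | 1.125 | 0.52 | 1.44 |
| 0.66 | 2.9375 | 1.405 | 0.67 | 1.75 |

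Over ρ from 0.4 to 0.8 the ratio runs from 1.32 to 2.27. On practice means, with ICC 0.02 and 33 per practice, it is 1.72 to 2.14 for ρ 0.5 to 0.66. These ratios do not depend on the utility SD.

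**Carry-through of a chance gap.** Slope times gap: a baseline utility gap of 0.02 shifts an unadjusted 24-month difference by 0.02 × 1.125 = 0.0225 (ρ 0.5) to 0.02 × 1.405 = 0.0281 (ρ 0.66) QALY.

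**Six-month interval QALYs.** Interval QALY = 0.25 × (utility at start + utility at end), with period terms and an intervention indicator. Further assumptions: utility SD 0.25 and 9, 9, 9 and 8 practices per arm.
- Ordinary regression: the SE falls from 0.00755 to 0.00449 at ρ 0.5 (1 − 0.00449/0.00755 = 41%) and from 0.00784 to 0.00378 at ρ 0.66 (1 − 0.00378/0.00784 = 52%). A simulation of 1500 replicates gave 0.00754 to 0.00451 (40%) and 0.00761 to 0.00377 (50%).
- Patient random-intercept working model: the SE is already about 0.0030 (ρ 0.5) or 0.0025 (ρ 0.66), and a common baseline covariate cuts it by only about 5%.
- Full covariance model with a common baseline slope: about 11% to 17%. It reaches about 39% if each interval has its own baseline slope and the equal-correlation structure is exact.

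The gain is therefore large for person totals and ordinary regression. It is modest where a common covariate is added to a model that already compares each person with themselves.

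**The case against.** The strongest reply is that the article is condensed and never calls the comparison raw. In the cost-effectiveness sentence the word mean belongs to costs only. A difference in quality of life or an incremental cost per QALY could equally be a regression estimate, and a bootstrap can be run around one. The multilevel model in the Analyses section covers all outcome measures, EQ-5D among them, and its estimates might be the ones carried into the economic evaluation. Covariate lists are often left to a fuller plan.

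Much of this stands. A reader might infer that the plan commits to raw means, but the documents do not say so. What the reply does not remove is the stated rule. If the Analyses model is carried over, its adjustment comes with the condition. If it is not, nothing is fixed. Neither reading makes baseline utility a standing covariate.

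Four stronger readings also fail.
- A reader might infer that the SE is far larger than needed under any analysis. The interval results show that this depends on the model.
- A comparison of 24-month totals between the first and last arms might look like the natural illustration. It is not planned, and the last arm itself starts the intervention at 18 months.
- One might say that chance gaps rival plausible QALY gains, or that the probability of cost-effectiveness becomes uninformative. The article gives no EQ-5D SD and no expected gain, so neither can be shown.
- Chance imbalance under randomisation is imprecision over repeated allocations, not systematic bias.

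**Conclusion.** The point holds in limited form. The Economic evaluation section names no baseline adjustment for QALYs and effects, and the only rule elsewhere is conditional, although the baseline values are to be collected.

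The size rests on three things the article does not settle: EQ-5D correlations, borrowed here from SF-12; equal correlation across visits; and how QALYs are attributed to usual-care and intervention time in a stepped wedge. The ratio of 1.44 to 1.75 describes a simple two-group comparison of person totals, so it indicates what is at stake rather than forecasting this trial's result. Even at the low end, always adjusting uses data already planned and guards against chance imbalance, so it is worth specifying.

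**What to change.** Add to the Economic evaluation section that:
- incremental QALYs and effects are estimated by regression that always includes the participant's value at study entry: EQ-5D utility for QALYs, and baseline SF-12, Katz or CANE for the matching effect;
- this does not depend on observed imbalance or on any baseline test;
- each bootstrap replicate refits the adjusted model, so that the ratios, planes and acceptability curves all rest on adjusted estimates.

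If the multilevel model of the Analyses section is meant to supply the economic effects, say so and drop the condition there for these outcomes. Estimating costs and effects jointly, for example by seemingly unrelated regression, and tabulating raw differences as a secondary display are optional.

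The cost is a few sentences of analysis text, with no new data, visits or participants.

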### Process evaluation

Alongside the intervention, we will conduct a mixed methods process evaluation. The process evaluation data will be used for summative purposes: Information will be used to investigate the extent to which the intervention was implemented as planned [47]. By exploring the ‘black box’ of the intervention, we aim to both gain an insight in (cost)effectiveness results and facilitate future implementation.

Process outcomes are level of implementation of the geriatric care model, barriers and facilitators to successful implementation, and the extent to which the intervention manages to achieve the transition necessary to target the three challenges in care for older adults, i.e. the untimely identification of health problems and care needs, the lack of client autonomy and the inadequate coordination between care professionals.

First, we will aim to assess the level of implementation using process constructs fidelity, dose delivered and dose received [47]. Further, we will seek to identify barriers and facilitators to successful implementation of the geriatric care model on cultural, operational and structural levels. To investigate whether the geriatric care model accomplishes the transition we intended, we will explore how older adults experience autonomy, how older adults and health care professionals experience the way care is coordinated during the intervention, and the extend to which the geriatric care model manages to be proactive in indentifying previously undetected health problems and care needs. Finally, in order to facilitate future implementation of the geriatric care model, we will investigate health care professionals’ learning experiences with the intervention. Table 2 offers an overview of process outcomes, used constructs and methods of data collection.

**Table 2 T2:** Process outcomes, constructs and methods of data collection

**Outcome**	**Concept**	**Methods**
**Level of implementation**	Fidelity	·*Semi-structured interviews* with geriatric team members, nurses, primary care physicians* ·*Focus groups* with practice nurses* · *Tailored care plans, time registration by practice nurses, registrations by expert geriatric teams, minutes of team meetings and training sessions*
	Dose delivered (completeness)	·*Tailored care plans* Total number of care plans delivered to clients during the intervention · *Tailored care plans (sample)* Average number of observations (RAI outcomes, nurses’ own observations) per care plan Average number of actions formulated per care plan Average number of care professionals involved in actions listed ·*Time registrations by practice nurses* Average amount of nurse’s working hours spent delivering intervention components (e.g. In-home assessments and care plan evaluation with clients, consultations with primary care physician, multidisciplinary consultations) ·*Registrations by expert geriatric teams* Number of multidisciplinary consultations organized
	Dose received (exposure, satisfaction)	·*Minutes of team meetings, registrations by expert geriatric teams* Number of training and coaching sessions and frequency of nurse’s attendance at these sessions Number of team meetings and frequency of nurse’s attendance at these meetings ·*Semi-structured interviews* with geriatric team members, nurses, primary care physicians* ·*Focus groups* with practice nurses, local stakeholders*
**Barriers and facilitators to implementation**	Barriers on cultural, operational and structural levels	·*Semi-structured interviews* with older adults, geriatric team members, nurses, primary care physicians* ·*Focus groups * with practice nurses, stakeholders*
**Extent to which transition is achieved**	Client autonomy	*·Semi-structured interviews * with older adults* ·*CCCQ questionnaire ***
	Coordination of care from the perspective of health professionals and patients	·*Semi-structured interviews * with geriatric team members, nurses, primary care physicians, older adults* ·*Focus groups * with practice nurses* ·*2 Items on QUOTE questionnaire ***
**Learning experiences of professionals**	Timely identification of health problems and care needs	·*Tailored care plans* Percentage of total number of RAI outcomes and nurses’ own registrations previously unknown to heath care professionals
		·*Semi-structured interviews * with geriatric team members, nurses, primary care physicians* · *Focus groups * with practice nurses, stakeholders*

* The qualitative study sample will include all older adults and health care professionals participating in the project, i.e. practice nurses, geriatric team members and primary care physicians and will be selected by means of a purposive (maximum variation) sampling procedure [48]; ** The quantitative study sample will include all older adults participating in the study; *CCCQ* Client-centred Care Questionnaire; *QUOTE* QUality Of care Through the patient’s Eyes.

Per process outcome, results of the qualitative and quantitative data collection will be analysed conform the requirements of a convergent parallel design. In a convergent parallel design, quantitative and qualitative data are concurrently collected in the same phase of the research process, and outcomes of both qualitative and quantitative analysis are combined during the overall interpretation [49].

## Discussion

The ACT-study aims to investigate the extent to which the geriatric care model has an effect on frail older adults’ quality of life. To our knowledge, it is one of the first European studies adopting a chronic care model approach to not only assess the effectiveness, but also the cost-effectiveness and the implementation process of an intervention for frail older adults living at home.

Carrying out the study in a real life primary care setting will provide insight into the generalizability of the geriatric care model, and may facilitate future implementation into routine practice. Moreover, the stepped-wedge design used in this study will allow us to introduce the intervention to all primary care practices participating in the study, so all frail older adults in the four allocation arms will eventually receive the geriatric care model. This has a number of advantages. First, the phased rolling out of the intervention will give us an opportunity to avoid having to withhold the geriatric care model from people who might benefit from it. Not only is this ethical argument compelling in itself, it has also played an important role in motivating primary care physicians to participate in the study. In addition, introducing the intervention to all four allocation arms offers methodological advantages. As mentioned in the effect evaluation paragraph, it will present us with the opportunity to take into account the effects of the duration of the intervention on outcome measures, Thus allowing us to differentiate between changes in outcomes due to time and due to the intervention.

In the years to come, the aging of the population will increasingly impose a strain on health care systems worldwide. It has become apparent that tackling emerging obstacles is essential in the securing of high-quality elderly care. By introducing the geriatric care model, we hope to contribute to the existing evidence on quality improvement and the effectiveness of integrated care models, and to present a solution for the many challenges facing care for older adults today.

## Abbreviations

ACT = Frail older adults: care in transition; ADL = Activities of daily living; ANOVA = Analysis of variance; CE = Cost-effectiveness; CU = Cost-utility; MICE = Multivariate imputation by chained equations; PRISMA = Program on research for integrating services for the maintenance of autonomy; RAI = Resident assessment instrument; QALY = Quality adjusted life years.
